#### Trial data collection

We will collect data related to trial screening, eligibility, consent, contact details and randomisation, questionnaire completion, withdrawal and intervention adherence.

#### Participant measures

##### Participant characteristics

We will collect data on NHS number, date of birth, marital status, employment status, education, menopausal status, number of children, year of diagnosis, stage of cancer at diagnosis, breast cancer type (primary, secondary), breast cancer treatment received, co-morbidities, hormone therapy regimen, supportive therapies used and previous exposure to psychotherapies.

##### Adherence Starts with Knowledge (ASK)-12 [45]

A 12-item, patient-report measure of barriers to medication adherence and adherence-related behavior. This is the planned future primary outcome in any future phase III trial.

##### McGill Quality of Life-Revised [46]

A 14-item, patient-report tool designed to measure physical well-being, physical symptoms, psychological symptoms, existential well-being and support, as well as overall quality of life of people with life-threatening illness.

##### Work and Social Adjustment Scale [47]

A 5-item self-report measure looking at how a specific illness/disorder impacts patient ability to function day to day with depression and/or anxiety as well as phobic disorders.

##### Hot Flash Related Daily Interference Scale (HFRDIS) [48]

A 10-item self-report questionnaire used to assess the impact of hot flashes on daily life and overall quality of life following breast cancer.

##### Multidimensional Assessment of Fatigue (MAF) [49]

A 16-item self-report scale that measures fatigue according to 4 dimensions; degree and severity, distress that it causes, timing of fatigue, and its impact on various activities of daily life.

##### PROMIS Pain Interference [50]

A 6-item self-report questionnaire measuring the consequences of pain over the last 7 days on relevant aspects of a person’s life, including engagement with social, cognitive, emotional, physical and recreational activities.

##### Day-to-Day Impact of Vaginal Aging Questionnaire: DIVA (part C) [51]

Part C (scale focusing on sexual functioning) of the DIVA questionnaire contains 8 self-report items relating to the impact of vaginal symptoms on functioning and well-being.

##### Generalised Anxiety Disorder questionnaire (GAD-7) [52]

The GAD-7 is a 7-item self-report anxiety questionnaire designed to assess the patients’ health status during the previous 2 weeks.

##### Patient Health Questionnaire-9 (PHQ-9) [53]

The PHQ-9 is a 9-item self-reported scale providing a valid and reliable measure of depression severity.

##### Functional Assessment of Cancer Therapy–Endocrine Symptoms [54]

The FACT-ES is a self-report quality of life questionnaire for people with cancer, consisting of 4 subscales which examine physical well-being with 7 items, social/family wellbeing with 7 items, emotional wellbeing with 6 items and functional wellbeing with 7 items as well as a series of items relating to additional concerns.

##### Valuing Questionnaire (VQ) [55]

A 10-item self-report questionnaire to measure aspects of psychological flexibility—mainly how consistently an individual has been living commensurate with their self-determined values.

##### Acceptability

Those participants recruited 3 months prior to the end of the recruitment phase and randomised to the ACT–based intervention will also complete items related to the acceptability of the intervention at 6 months post-randomisation only. Items ask about the acceptability of the different components of ACTION and whether participants found it useful.

##### Borkovec and Nau Acceptability Questionnaire (B&N) [56]

Three items adapted from the B&N will be collected, based on the wording used in the OBI study [57]. This is an additional measure of acceptability and will be used within the progression criteria.

##### UK Cancer Costs Questionnaire [58]

We adapted the UK Cancer Costs Questionnaire to assess services accessed by the participants at baseline and follow-up time points.

#### Therapist measures

##### ACT Knowledge Questionnaire (ACTKQ) [43]

The ACTKQ is an assessment of therapist knowledge of the principles of ACT. It has 16 items.

##### Procedural fidelity checklist

The procedural fidelity checklist was designed for the ACTION trial for therapists to self-rate whether or not they undertook crucial intervention procedures that were previously outlined in training and in the manual. It has 26 items, and is rated at the end of each of the four sessions.

##### ACT Fidelity Measure (ACT-FM) [44]

The ACT-FM is a measure of therapist fidelity to ACT principles when delivering treatment. There are 25 items capturing pre- and pro-scribed therapist behaviours when delivering ACT. The ACT-FM is scored when reviewing the therapy tapes of a clinician delivering ACT.

#### Site measures

##### Intervention adherence

Intervention adherence data will be collected from the delivering site and will include the number of sessions attended and the number of participants in the group sessions.

##### Treatment as usual monitoring

Treatment as usual will be monitored at all recruitment sites. It will include data at the service level, including services offered, to allow for an assessment of treatment as usual. This data will be collected at the end of recruitment with sites asked to report treatment as usual throughout the recruitment phase.

### Sample size

As the study is randomised and we wish to obtain a preliminary estimate of effectiveness in relation to demonstrating how the intervention affects medication adherence, we have used methods developed for phase II screening trials in oncology [59] in which preliminary and non-definitive randomised treatment comparisons are made, carefully adjusting the false-positive (a) and false-negative (ß) error rates so the target treatment effect is appropriate while the sample size remains restricted. Allowing for 25% loss to follow-up and using a 1-sided *t* test with a significance level of 20% will allow us to detect an effect size of 0.432 with 65% power using a sample of 80 patients. The sample size must be sufficient to establish consent and dropout rates (Objective i) and test trial protocols and acceptability (Objectives ii–iii). A sample size of *N* = 40 per arm will be sufficient to meet these aims [60–62].

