## Methods

### Design

This is a multi-site, exploratory, two-arm, individually randomised pilot RCT with a nested qualitative study. Eighty women with early stage breast cancer will be randomised (1:1) to receive treatment as usual or treatment as usual plus the ACTION intervention. The study has been approved by the York and South Yorkshire Health Research Authority Research Ethics Committee (20/YH/0104), and is a registered clinical trial (ISRCTN12027752). The study is presented according to recommendations of the SPIRIT [40] and CONSORT extension for pilot and feasibility trials [41] (Appendix 1). The intervention being evaluated is described using the TIDieR checklist [42] (Appendix 1).

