### Analysis

A detailed statistical analysis plan will be written before any analysis is undertaken. The analysis will focus on descriptive statistics and confidence interval estimation rather than formal hypothesis testing and no formal evaluation of safety or efficacy of the study interventions will be conducted. All analyses will be undertaken on the intention-to-treat population, with all participants included in the analysis according to their randomised allocation, and regardless of non-adherence to the intervention or withdrawal from the study. Final analysis will be conducted once all available outcome data is received.

Descriptive summaries will be presented overall, by arm and by site (where relevant) using appropriate frequencies and summary statistics. Outcome measures will be scored according to relevant scoring manuals. To generate evidence of proof of principle, the mean change from baseline in the three and 6-month ASK-12 scores in both arms will be reported, together with a range of confidence intervals around the main estimate to inform us as to the likelihood of where the ‘true’ estimate may lie. Analysis will adjust for the minimisation factors.

The trial is not powered to provide a precise estimate of the level of clustering relating to therapist effects, but we may be able to investigate this effect. If a sufficient number of therapists are involved in delivering the intervention, we will estimate the intraclass correlation coefficient and produce a range of confidence intervals (e.g. 95%, 67% and 51%) around this to inform the sample size of the definitive trial.

The semi-structured interviews will be analysed using thematic analysis [63].

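### The sample-size figures do not fit together: a 1-sided 20% t test with 30 evaluable per arm has about 80% power at an effect size of 0.432, not 65%

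*Protocol article*

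**What the plan says.** The Sample size section adopts a phase II screening approach from oncology, in which the two error rates are deliberately relaxed so that a small randomised comparison can still give a preliminary signal on medication adherence. The calculation is one sentence. It opens "Allowing for 25% loss to follow-up and using a 1-sided" t test, and states that this "test with a significance level of 20% will allow us to detect an effect size of 0.432 with 65% power", with a sample of 80. The Design section gives the allocation: "Eighty women with early stage breast cancer will be randomised (1:1"). The Sample size section adds, as a separate justification for the feasibility aims, that "40 per arm will be sufficient to meet these aims".

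No design effect, covariate correlation or other adjustment enters the calculation. Clustering appears only in the Analysis section, as something that might be estimated: "The trial is not powered to provide a precise estimate of the level of clustering relating to therapist effects".

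For the ASK-12 adherence score, the Analysis section plans to report mean change from baseline at three and six months, "together with a range of confidence intervals around the main estimate". It says that the emphasis is on description and interval estimation, not formal testing.

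**The concern.** The sentence fixes every input of a two-sample t test: number randomised, loss, allocation, sidedness, significance level, standardised effect and power. Any one of them therefore follows from the rest, and the printed set does not close.

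The screening approach exists to choose the false-positive and false-negative rates openly. Those two rates tell a reader how much weight a positive or a null adherence signal from this pilot can bear. If the test, the effect and the power disagree, one of the two stated rates is wrong by a factor of nearly two, and the article does not show which.

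**Working it through.** **Inputs (Sample size and Design sections)**
- Randomised: 80, allocated 1:1, so 40 per arm.
- Loss to follow-up 25%: 80 × 0.75 = 60 evaluable, n = 30 per arm, df = 58.
- Test: 1-sided t test at 20%.
- Standardised effect d = 0.432 (SD = 1); stated power 65%.

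**Method.** Exact noncentral t. The standard error of the standardised difference is √(2/n) = √(2/30) = 0.2582, so the noncentrality parameter at d = 0.432 is 0.432 / 0.2582 = 1.673.

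**Step 1. The test as named.** The 1-sided 20% critical value on 58 df is 0.848.
- Power at 0.432 = P(T > 0.848 | noncentrality 1.673) = **79.6%**, against 65% stated. Normal check: Φ(1.673 − 0.842) = Φ(0.831) = 79.7%.
- Detectable effect at 65% power = **0.318**, against 0.432 stated. Normal check: (0.842 + 0.385) × 0.2582 = 0.317.
- Sample size for 1-sided 20%, d = 0.432 and 65% power: 17 per arm (power 65.9%; 16 per arm gives 64.5%). That is 34 evaluable, and 34 / 0.75 = 45.3, so 46 randomised, against 80 stated.

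The printed figure is not reproduced.

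**Step 2. The same sentence read as 2-sided 20%.** The critical value is ±1.296.
- Detectable effect at 65% power = **0.4323** counting both tails (0.4335 counting the upper tail only; normal approximation 0.430).
- Power at 0.432 = **65.0%** (64.8% upper tail only).
- The normal sample-size formula gives 30 per arm, 60 evaluable, and 60 / 0.75 = 80.

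This recovers 0.432, 65% and 80 together. In the beneficial direction it is a 1-sided 10% test.

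**Step 3. Other explanations tried**

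| Explanation, keeping the 1-sided 20% test | Result |
|---|---|
| 32 per arm (loss taken as 80/1.25 = 64) | detects 0.308 at 65% power |
| 40 per arm (loss ignored) | detects 0.275 at 65% power |
| Power misprinted, true value 80% | detects 0.436, near 0.432 but not equal |
| Unstated inflation for clustering | needs a design effect of about 1.85 in both arms, or about 2.7 in the intervention arm alone; none is stated |

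The two alternatives on loss move away from 0.432. A misprinted power comes close. Of the variants tried, only the 2-sided 20% test gives 0.432 to three decimals.

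**Step 4. Which error rate is affected**

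| Reading | False positive, beneficial direction | False negative at 0.432 |
|---|---|---|
| As printed | 20% | 35% |
| 2-sided 20% (1-sided 10%) | about 10% | 35% |
| 1-sided 20%, 30 per arm | 20% | about 20% (100 − 79.6 = 20.4) |

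Each corrected reading changes one rate and leaves the other as printed.

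**The case against.** The strongest reply is that little depends on this sentence. If the 1-sided 20% test is what was meant, 80 women give more power than claimed, so the error is on the safe side. The Analysis section plans estimation, the primary endpoints in Table 5 are feasibility measures with proof of principle listed as secondary, and 40 per arm is justified separately for the feasibility aims. All of this stands. It limits the weight of the point, but it does not make the figures agree. Nor is this a detail left to the analysis plan: it is a stated calculation that does not reproduce.

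A reader might also infer more than the article supports, in four ways.

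- *That the calculation was certainly 2-sided.* It is the best numerical match, but the article does not show which element slipped, and a misprinted power remains possible.
- *That both error rates are misreported.* They cannot be. A false-positive rate of 10% needs the 2-sided reading, and a false-negative rate of 20% needs the 1-sided one.
- *That the decision to proceed to phase III carries the wrong risk.* The Abstract lists proof of principle on adherence among the progression criteria, but Table 6 is not reproduced in the text available. Whether that criterion uses a test, an interval, a point estimate or a direction cannot be seen.
- *That the interval levels are mismatched.* The 95%, 67% and 51% levels in the Analysis section are examples for the intraclass correlation and were not tied to the sample-size significance level. The levels for ASK-12 can properly be left to the analysis plan.

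**Conclusion.** The point holds in a narrow form. Sidedness, significance level, effect size and power in the Sample size section are mutually inconsistent. Under the named test, power at 0.432 is understated by about 15 percentage points (79.6% against 65%); equivalently, the detectable effect at 65% power is overstated (0.432 against 0.318). A 2-sided 20% calculation is the likely but unproven source.

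The result assumes 30 evaluable per arm, a plain two-sample t test, and no design effect or covariate adjustment, which is all that the article states. Severity is moderate: the trial is not undersized under the named test, no conclusion about feasibility changes, and the planned analysis is estimation. What needs correcting is the stated operating characteristics of the adherence comparison.

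**What to change.** Retrieve the sample-size calculation on file, establish which element was misprinted, and restate the sentence as one consistent set with 80 randomised and 25% loss unchanged. Two forms close:

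- 2-sided 20% (equivalently 1-sided 10%), effect size 0.432, 65% power; or
- 1-sided 20%, effect size 0.432, about 80% power (equivalently 0.32 at 65% power).

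If an adjustment such as a design effect was in fact applied, state it and its value instead. Carry the corrected set into the analysis plan so that the two documents agree.

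The cost is one corrected sentence. It needs no more patients, and recruitment and data collection are unaffected.

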### Nested qualitative study

Following completion of the study, all participants assigned to the intervention group will be invited to participate in telephone interviews with a researcher. Interviews will focus on the acceptability of the intervention, trial procedures and outcome measures. We will seek to identify components of the intervention that were perceived as particularly helpful or unhelpful to participants. If aspects of the trial are considered unacceptable or unhelpful, questions will be asked to resolve some of these issues in preparation for a phase III RCT.

The therapists delivering the intervention will also be invited to participate in semi-structured telephone interviews. These will inquire about therapist’s experiences of delivering the intervention, the practicability of the intervention (within NHS contexts), training and ways to improve the programme.

### Analysis

A detailed statistical analysis plan will be written before any analysis is undertaken. The analysis will focus on descriptive statistics and confidence interval estimation rather than formal hypothesis testing and no formal evaluation of safety or efficacy of the study interventions will be conducted. All analyses will be undertaken on the intention-to-treat population, with all participants included in the analysis according to their randomised allocation, and regardless of non-adherence to the intervention or withdrawal from the study. Final analysis will be conducted once all available outcome data is received.

Descriptive summaries will be presented overall, by arm and by site (where relevant) using appropriate frequencies and summary statistics. Outcome measures will be scored according to relevant scoring manuals. To generate evidence of proof of principle, the mean change from baseline in the three and 6-month ASK-12 scores in both arms will be reported, together with a range of confidence intervals around the main estimate to inform us as to the likelihood of where the ‘true’ estimate may lie. Analysis will adjust for the minimisation factors.

The trial is not powered to provide a precise estimate of the level of clustering relating to therapist effects, but we may be able to investigate this effect. If a sufficient number of therapists are involved in delivering the intervention, we will estimate the intraclass correlation coefficient and produce a range of confidence intervals (e.g. 95%, 67% and 51%) around this to inform the sample size of the definitive trial.

The semi-structured interviews will be analysed using thematic analysis [63].

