Following informed consent, confirmation of eligibility and receipt of the baseline questionnaire, participants will be randomised by the research site using the University of Leeds Clinical Trials Research Unit (CTRU) randomisation system. Participants will be randomised on a 1:1 basis to receive either treatment as usual or treatment as usual plus the ACTION intervention and will be allocated a trial number. A computer-generated minimisation programme that incorporates a random element will be used to ensure treatment groups are well-balanced for the following stratification factors: recruiting site, recruitment route (recently completed treatment vs. experiencing medication problems vs. retrospective screening), participant age (≤ 50 years vs. > 50 years and < 70 years vs. ≥ 70 years).

Participants, therapists, research nurses/delegates at site, participant’s GP and staff at the Clinical Trials Research Unit (CTRU) will be not be blinded to the randomised allocation. Following randomisation the research nurse will notify the participant of their allocation, and the therapists will be informed about participants allocated to the intervention arm.

All participants will be requested to complete a follow-up questionnaire at 3 months post-randomisation. Participants recruited at least 3 months prior to the end of the recruitment period will also be invited to complete a questionnaire at 6 months post-randomisation. Participants will have the option to receive questionnaires by post or online. Non-responders will be reminded using postal, telephone, online and text prompts.

A clinician may decide that a participant should be withdrawn from the intervention if there is reason to believe they have become unsuitable for the study. Participants can also withdraw from one or more of the following: intervention, data collected from them via questionnaires or data about them from medical records.

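### The ASK-12 analysis names change from baseline and the minimisation factors but not baseline ASK-12 as a covariate; run as written, it gives up precision

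*Protocol article*

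**What the plan says.** The Analysis section sets out three things for ASK-12, the planned primary outcome of the later phase III trial.

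- Form of the outcome: "the mean change from baseline in the three and 6-month ASK-12 scores in both arms will be reported", together with a set of confidence intervals around the main estimate.
- Covariates: "Analysis will adjust for the minimisation factors". Under Study processes these are "recruiting site, recruitment route (recently completed treatment vs. experiencing medication problems vs. retrospective screening), participant age", the last in three bands. Baseline ASK-12 is not a minimisation factor.
- Purpose: the emphasis is on "descriptive statistics and confidence interval estimation rather than formal hypothesis testing".

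The same section defers detail: "A detailed statistical analysis plan will be written before any analysis is undertaken".

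Table 3 schedules ASK-12 at baseline, 3 months and 6 months. The baseline score precedes allocation: "Following informed consent, confirmation of eligibility and receipt of the baseline questionnaire, participants will be randomised".

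**The concern.** Baseline ASK-12 is likely to be the strongest predictor of follow-up ASK-12 that the trial holds. As the article reads, it enters the analysis only by subtraction. Subtracting baseline fixes its weight at 1, whereas using it as a covariate lets the data set the weight. The fixed weight costs precision whenever the correlation between the two scores is below 1.

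The sentence on mean change is more than a per-arm summary. It is offered as evidence for proof of principle, which objective (iv) in the Background describes as exploring change between the groups. A plain summary by arm would also need no adjustment for minimisation factors, so a between-arm model is evidently meant. The Abstract lists proof of principle for change in adherence among the grounds for moving to phase III, so this estimate informs that decision. Because the article relies on interval estimation, the width of the interval is what matters.

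**Working it through.** **Inputs from the article (Sample size section):** 80 randomised 1:1, 25% loss, effect size 0.432, one-sided t test at 20%, stated power 65%. The number analysed follows: 80 × 0.75 = 60, or 30 per arm. This fits the 3-month comparison. The 6-month questionnaire goes only to earlier recruits, so that number may be smaller.

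**Assumed input:** r, the within-arm correlation between baseline and follow-up ASK-12. It is not in the documents, so a range of 0.3 to 0.9 is shown.

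**Step 1: the plan's own figure.** With 30 per arm and 0.432, the noncentrality is 0.432 × √(30/2) = 1.673. At one-sided 20% the noncentral t distribution gives power of 79.6%, not 65%. The stated 65% appears at two-sided 20% (64.8%). That mismatch is a separate matter. It is noted here because it decides which power figures may be used in step 4.

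**Step 2: variances.** With equal SD s at both times:

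- change score: s² × 2(1−r)
- baseline as covariate: s² × (1−r²)
- ratio: (1−r²) / [2(1−r)] = (1+r)/2

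The direction does not depend on equal SDs. With baseline SD s0 and follow-up SD s1, the change-score variance minus the adjusted variance is (s0 − r·s1)², which is never negative.

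**Step 3: size with 60 analysed.** Interval width scales with the square root of the ratio. The equivalent number is 60 divided by the ratio.

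| assumed r | variance ratio | interval narrower by | 60 women with baseline adjustment equal, on the change score |
|---|---|---|---|
| 0.3 | 0.65 | 19% | 92 |
| 0.5 | 0.75 | 13% | 80 |
| 0.7 | 0.85 | 8% | 71 |
| 0.9 | 0.95 | 2.5% | 63 |

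Example at r = 0.5, in SD units: the standard error is √(1.00 × 2/30) = 0.258 for the change score and √(0.75 × 2/30) = 0.224 with baseline adjustment.

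The same loss can be seen through chance imbalance. The baseline difference between arms has SD √(2/30) = 0.258 SD. For an observed baseline difference D, the change-score contrast shifts by −(1−r)D. At r = 0.5 and D = 0.258 that is 0.129 SD. Over repeated randomisations the shift averages to zero.

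**Step 4: power at the stated one-sided 20%, 30 per arm.** The article does not say which SD the 0.432 refers to, so both readings are given.

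| assumed r | 0.432 in raw SD: change score | 0.432 in raw SD: with baseline | 0.432 in change-score SD: change score | 0.432 in change-score SD: with baseline |
|---|---|---|---|---|
| 0.3 | 71.5% | 81.8% | 79.6% | 89.0% |
| 0.5 | 79.6% | 86.1% | 79.6% | 86.1% |
| 0.7 | 90.5% | 93.2% | 79.6% | 83.3% |
| 0.9 | 99.8% | 99.9% | 79.6% | 80.8% |

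Every entry exceeds the stated 65%.

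**The case against.** The strongest reply is that the article does not exclude baseline ASK-12. It names the minimisation factors and says nothing of further covariates, and the model is left to an analysis plan that was not available. Reporting mean change by arm is also compatible with baseline adjustment: a model of change with baseline as a covariate gives the same treatment estimate as a baseline-adjusted model of the follow-up score. This stands. A reader might infer that the plan adjusts for the minimisation factors alone and rejects baseline, but the text does not say so. What remains is that an article which names an adjustment set invites the analysis plan to copy it.

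The second reply is that the size of the loss is unknown. This also stands. At r = 0.9 the gain is small, and estimating the extra slope uses a little of it. A reader might infer that the change score does worse than ignoring baseline altogether. That needs r below 0.5, and nothing in the documents supports such a value.

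The third reply is that the comparison is exploratory: proof of principle is a secondary endpoint in Table 5, and no formal evaluation of efficacy is planned. This limits the consequence but does not remove it, since the intervals are the intended product.

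**Conclusion.** The point holds as one of efficiency. If the ASK-12 comparison is run as the article words it, the between-arm estimate is unbiased under randomisation but its intervals are wider than they need be. With baseline adjustment they would be narrower by about 19% at r = 0.3, 13% at 0.5, 8% at 0.7 and 2.5% at 0.9. This rests on an assumed r, on equal SDs for the exact ratios, and on the analysis plan not already including baseline. Since that plan was not available, confidence is moderate.

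Three stronger readings are not supported:

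- **Bias.** The contrast is over-corrected only conditionally on an observed baseline imbalance. It is not biased.
- **A power shortfall.** At the stated one-sided 20%, the change score exceeds 65% at every r shown. A shortfall appears only if the level is read as two-sided 20%, which is not what the Sample size section says.
- **That this estimate drives progression.** It is one of several grounds, and the Table 6 thresholds were not legible in the copy reviewed.

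**What to change.** State in the analysis plan, and in the article's Analysis section if it is revised, that the between-arm ASK-12 difference at 3 and 6 months is estimated with baseline ASK-12 and the minimisation factors as covariates. Either ANCOVA at each time or one repeated-measures model covering both would serve. Take the set of confidence intervals from that model, and keep mean change by arm as description. Treat the other questionnaire outcomes measured at baseline in the same way.

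The cost is one line of wording and one degree of freedom per model, with no new data and no added burden on participants. If the analysis plan already includes baseline ASK-12, confirming it is enough.

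### The main ASK-12 estimate is stated as change from baseline at each visit; one repeated-measures model with baseline ASK-12 as a covariate would be more precise at no cost

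*Protocol article*

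**What the plan says.** The Analysis section of the protocol article defines the proof-of-principle result for the planned phase III primary outcome: "the mean change from baseline in the three and 6-month ASK-12 scores in both arms will be reported", with several confidence intervals around the estimate. It adds that "Analysis will adjust for the minimisation factors". Under Study processes those factors are recruiting site, recruitment route and age group.

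The same section says that analyses follow the intention-to-treat principle, described as "with all participants included in the analysis according to their randomised allocation, and regardless of non-adherence to the intervention or withdrawal from the study". It sets the inferential level, "The analysis will focus on descriptive statistics and confidence interval estimation rather than formal hypothesis testing", and defers detail: "A detailed statistical analysis plan will be written before any analysis is undertaken".

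On data collection, Study processes states that "All participants will be requested to complete a follow-up questionnaire at 3 months post-randomisation". Only women who enter three months or more before recruitment closes "will also be invited to complete a questionnaire at 6 months post-randomisation", and Table 3 repeats this restriction. The baseline questionnaire must be received before randomisation. The Sample size section works with 80 women, "Allowing for 25% loss to follow-up".

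**The concern.** A change score exists only for a woman who returned that visit's questionnaire. If the stated summary is computed visit by visit, three things follow.

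- Subtracting baseline is a less efficient use of it than adjusting for it, and baseline ASK-12 is not among the named adjustment factors.
- A woman with a 3-month score and no 6-month score adds nothing to the 6-month estimate, although her 3-month score carries information about it.
- The 6-month estimate comes from a smaller set than the 3-month one, so moving from one visit mean to the next mixes time with a change of sample.

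At stake is the precision of the estimate that feeds the proof-of-principle progression criterion and informs a phase III trial. There is also some exposure to bias if 6-month response depends on earlier outcome in an arm-specific way, which is conceivable when participants are unblinded and ASK-12 is self-completed.

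**Working it through.** **Inputs from the article.** 80 women randomised 1:1; 25% loss; recruitment from 04/2021 to about 09/2022, so 17–18 months; no 6-month invitation for women recruited in the last 3 months; target effect 0.432. The stated 65% power does not reproduce for a one-sided 20% test with 30 per arm (79.6%), but does for a two-sided 20% test (64.8%). Nothing below depends on this.

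**Assumptions, not in the article.** Even accrual; 25% loss at each visit among those asked; equal SDs, set to 1; the same baseline correlation ρ = 0.5–0.6 at both visits; 3-to-6-month correlation ρ₃₆ = 0.6–0.8.

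**Step 1: women contributing.**
- 3 months: 80 × 0.75 = 60.
- Not invited at 6 months: 80 × 3/18 = 13.3 (80 × 3/17 = 14.1), so 13–14 women.
- 6 months: 80 × 15/18 × 0.75 = 50.0 (80 × 14/17 × 0.75 = 49.4).
- SE at 6 months relative to 3 months, same estimator: √(60/50) = 1.10.

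**Step 2: baseline adjustment against change scores, same women.** The variance of a change score is 2(1 − ρ); the residual variance given baseline is 1 − ρ². The SE ratio is √[(1 − ρ²)/(2(1 − ρ))] = √[(1 + ρ)/2].
- ρ = 0.5: √0.75 = 0.866, an SE 13.4% lower.
- ρ = 0.6: √0.80 = 0.894, an SE 10.6% lower.

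**Step 3: linking the visits.** Let r be the 3-to-6-month correlation given baseline, r = (ρ₃₆ − ρ²)/(1 − ρ²). If the n₆ women seen at 6 months are nested in n₃ = 60 seen at 3 months, the SE ratio of the joint model to a visit-wise baseline-adjusted analysis is about √[1 − r²(1 − n₆/n₃)].

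| ρ | ρ₃₆ | r² | n₆ = 50 | n₆ = 45 | n₆ = 37.5 |
|---|---|---|---|---|---|
| 0.6 | 0.6 | 0.141 | 1.2% lower | 1.8% | 2.7% |
| 0.5 | 0.6 | 0.218 | 1.8% | 2.8% | 4.2% |
| 0.6 | 0.8 | 0.473 | 4.0% | 6.1% | 9.3% |
| 0.5 | 0.8 | 0.538 | 4.6% | 7.0% | 10.7% |

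Here 37.5 = 66.7 × 0.75 × 0.75 is the number with both visits if non-response is independent across visits.

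**Step 4: total against change scores.** Multiply the ratios of steps 2 and 3. Smallest gain: 0.894 × 0.988 = 0.884, so 12% lower. Largest gain: 0.866 × 0.893 = 0.774, so 23% lower. These formulas ignore the small cost of estimating the covariance. Simulations with 80 women gave 10–18% with 45–50 women at 6 months and 14–22% with about 37 women having both visits; against visit-wise baseline-adjusted analysis they gave 1–7% and 3–11%. In every row the baseline step supplies most of the total.

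**Step 5: bias.** The true effect was 0.432, and intervention women with worse 3-month scores were made to skip 6 months more often (log-odds 0.5–1.0 per SD). Across the simulations, visit-wise change scores gave 0.44–0.51, visit-wise baseline-adjusted analysis 0.47–0.53 and the joint model 0.43–0.44. The change-score bias is thus at most 0.51 − 0.432 ≈ 0.08 SD. For scale, with about 22 women per arm at 6 months the change-score SE is √[2(1 − ρ)] × √(2/22) = 0.27–0.30. Adjusting for baseline alone does not remove this bias; using the 3-month score does.

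**The case against.** The strongest reply is that the article names a quantity to report, not an estimator. A repeated-measures model also yields mean change by visit, adjustment for minimisation factors implies some model, and its form and the handling of missing data normally belong in the analysis plan, which is not shown. This stands in part. A reader might infer that women missing a visit are excluded, but the article states no complete-case rule, and that reading is not supported. What remains is that the summary it does state is change from baseline, with a listed adjustment set that omits baseline ASK-12.

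A reader might also infer a contradiction between 25% loss and the inclusion of all participants. The wording can equally mean analysis by allocation, and the section also refers to available outcome data. A model using women with at least one follow-up score would still omit those with none, so this is not a fault that the fix cures.

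Nor do the two visits describe different women. Everyone is asked at 3 months and the 6-month invitees are a subset. The cut-off is a calendar date applied alike to both arms, so it does not itself bias the between-arm contrast. The article does not promise a 3-to-6-month comparison.

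On size, the gain from linking visits is small, and the bias needs an assumed arm-specific mechanism. A count of about 72 of 80 women with any follow-up score requires non-response independent across visits. If loss is nested, that number is about 60, so the higher count should not be relied on. All of this stands and limits the weight of the point.

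**Conclusion.** The point holds as an improvement to the stated estimate. Taken as visit-wise change adjusted only for site, route and age, the 6-month result uses about 50 of 80 women, leaves the 3-month scores of the others unused and handles baseline inefficiently. One repeated-measures model lowers the 6-month SE by roughly 10–20% against change scores, mostly through baseline adjustment, and by about 1–11% against a visit-wise baseline-adjusted analysis. These figures rest on the assumed correlations of 0.5–0.8, even accrual and 25% loss at each visit. Bias is conditional and modest: up to about 0.08 SD for change scores, and only where 6-month non-response depends on the 3-month score differently by arm.

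The estimate is secondary and exploratory in a pilot with feasibility primary endpoints and no formal efficacy evaluation. The stronger conclusions, that women are dropped, that the intention-to-treat statement is breached or that the trial's contrast is biased by design, do not follow from the article.

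**What to change.** In the analysis plan, and in the protocol at its next revision:

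- Make the main ASK-12 estimate the between-arm difference at 3 and at 6 months from one likelihood-based repeated-measures model with arm, visit, arm-by-visit, baseline ASK-12 and the minimisation factors, and an unstructured covariance for the two visits. Report it with the planned range of confidence intervals.
- Keep observed mean changes by arm and visit as description, each with the number of women contributing, and note that late recruits are not asked at 6 months.
- Describe the analysed set as randomised women with at least one follow-up ASK-12, analysed as allocated, and report how many have none.

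The cost is wording and a standard model. Baseline ASK-12 is already collected before randomisation, so no new data and no further participants are needed.
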